**PRIMARY**			
Patient-reported Health-Related Quality of Life (HRQOL) outcomes	Improved	HRQOL scores, measured by the EQ-5D-5L at 12 weeks	Examine the distributions/ Wilcoxon rank sum test/regression

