### Outcomes

#### Primary outcome

The primary outcome is difference in HRQOL scores between the treatment groups, as measured by the EQ-5D-5L questionnaire at week 12.

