#### Enrollment and baseline

Potential participants will be screened to determine if they meet the eligibility criteria. Potential participants who meet the eligibility criteria will be approached by a trial coordinator to determine if they agree to participate. If they agree, they will be asked to and sign the PICF. Once the PICF is signed, they will be considered enrolled, and the participant will be randomized, asked to complete the Trial Health Questionnaire and be provided a Study Diary.

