### Sample size

#### Primary outcome in Phase A

The sample size for the primary outcome in Phase A was calculated based on the Minimally Important Difference (MID) of the EQ-5D-5L derived utility scores among lung cancer patients in the United States of America (USA). The index-based score is typically interpreted along a continuum where 1 represents full health and 0 represents dead, with some health states being worse than dead (<0). A MID of 0.07 and SD of 0.16 is considered clinically significant for this patient population [13]. The MID of 0.07 was considered clinically significant for this patient population because in 2007, Pickard et al. had reported that for EQ-5D utility scores in the USA, MIDs, grouped by performance status, ranged from 0.07 to 0.09 for all cancers and for lung cancer, but when based on FACT-G quintiles, MIDs were 0.06 to 0.07 in all cancers, and 0.05 to 0.06 in lung cancer [13]. A sample size of 166 patients, with 83 patients per arm will ensure detection of this difference with 80% power at a level of significance of 0.05. A 10% drop out rate was used to account for those potential withdrawals, therefore a total of 186 participants will be recruited to the trial, 93 participants per trial arm.

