## Assignment of interventions: Allocation

### Sequence generation

A statistician who is a member of the Biostatistics Unit at St. Joseph’s Healthcare Hamilton, generated the randomization sequence using SAS [14]. Randomization was stratified by surgeon. For each surgeon, a unique randomization sequence using the random permuted-block design (with blocks of varying sizes) to randomize patients in a 1:1 ratio to one of two intervention arms, VATS-Lobectomy or RTS-Lobectomy, was generated. This method ensures that an approximately equal number of patients will be allocated to each treatment group.

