## Statistical methods

### Statistical methods for primary and secondary outcomes

Baseline characteristics of both treatment groups will be compared to ensure homogeneity in the patient population. Descriptive statistics will be reported by treatment group where categorical variables will be reported as counts (percentages) and continuous variables as mean (standard deviation) or as median (25^th^ percentile, 75th percentile). All analyses of primary and secondary outcomes will be carried out based on the intention-to-treat principle. Unadjusted comparisons of continuous outcome measures will be carried out using an independent t-test or the Wilcoxon rank-sum test if the assumptions of the t-test were violated. Unadjusted comparisons of categorical outcome measures will be computed using the chi-squared test, or the Fisher’s exact test if any of the expected values in the contingency table is less than 5, or McNemar’s test. For adjusted analyses, multivariable logistic regression analyses will be used for binary outcomes and multivariable linear regression for continuous outcomes. The results of comparisons between groups will be presented as mean differences for continuous outcomes and relative risks or odds ratios for binary outcomes, with corresponding 95% confidence intervals and associated p-values. ANOVA will be used for repeated measures. Survival will be compared using the Kaplan-Meier method and cox proportional hazard models. Survival curves will be compared using the Log-rank test. P-values will be reported to three decimal places with p-values less than 0.001 reported as p < 0.001. All analyses will be performed using SAS. Table 3 provides a summary of the variables, measures and methods of analysis.

**Table 3 pone.0261767.t003:** Variables, measures and methods of analysis.

Variable/Outcome	Hypothesis*	Outcome	Method of Analysis

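### The primary week-12 EQ-5D-5L analysis is an open menu that conflicts with the rest of the Protocol article; one mean-difference regression should be named before unblinded Phase A data are seen

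*Protocol article*

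**What the plan says.** All references are to the Protocol article.

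- **Outcome** (Primary outcome): "The primary outcome is difference in HRQOL scores between the treatment groups, as measured by the EQ-5D-5L questionnaire at week 12".
- **Sizing** (Sample size, Primary outcome in Phase A): "A MID of 0.07 and SD of 0.16 is considered clinically significant for this patient population"; "A sample size of 166 patients, with 83 patients per arm will ensure detection of this difference". The stated power is 80% and the significance level 0.05.
- **Primary method** (Table 3, primary row): "Examine the distributions/ Wilcoxon rank sum test/regression".
- **General rule** (Statistical methods for primary and secondary outcomes): "Unadjusted comparisons of continuous outcome measures will be carried out using an independent t-test or the Wilcoxon rank-sum test", the latter as a fallback when t-test assumptions fail, with no criterion given. The same section provides multivariable linear regression for adjusted analyses, names no covariates, and has continuous results reported as mean differences with 95% CIs and p-values.
- **Primary analysis section**: an effect size on the utility scores is to be used for the comparison. No test is named.
- **Sensitivity row of Table 3**: the same week-12 outcome, by t-test or linear regression with multiple imputation.
- **Design data**: "Randomization was stratified by surgeon" (Sequence generation). The Trial Health Questionnaire, which contains the EQ-5D-5L, is completed at baseline (Baseline data collection; Trial health questionnaire). In Enrollment and baseline the order is that "the participant will be randomized, asked to complete the Trial Health Questionnaire".

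**The concern.** A primary analysis should be one method aimed at one quantity, fixed in advance. Here the primary cell starts with inspecting the data, then offers a rank test or a regression with no stated covariates. The general text points to a third method, the t-test, which the primary row omits and the sensitivity row lists.

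Two things are at stake:

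- The methods answer different questions. The t-test and linear regression address a difference in means. The rank-sum test addresses whether scores in one arm tend to exceed those in the other. The headline p-value could therefore disagree with the mean difference printed beside it.
- Baseline utility and surgeon are already recorded and would sharpen the comparison, but nothing shown commits the trial to using them.

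**Working it through.** **1. Reproduce the plan's figure.** Inputs: difference 0.07, SD 0.16, 80% power, level 0.05 (sidedness not stated).

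- n per arm = 2 × [SD × (z₀.₉₇₅ + z₀.₈₀) / difference]² = 2 × [0.16 × (1.960 + 0.842) / 0.07]² = 82.01, rounded up to 83.
- The noncentral t calculation gives 82.98, also 83, with power 80.0% at 83 per arm.
- A one-sided test would need only 65, so the plan used a two-sided test.
- Dropout: 83 / 0.90 = 92.2, rounded up to 93 per arm, 186 in all.

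The figure reproduces as an unadjusted two-sided comparison of means.

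**2. Which test carries the primary p-value?**

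| Place | t-test | Wilcoxon | Regression |
|---|---|---|---|
| Statistical methods text | default, unadjusted | fallback, no criterion | for adjusted analyses, covariates unnamed |
| Table 3, primary row | absent | listed | listed, unspecified |
| Primary analysis section | not named | not named | not named |
| Table 3, sensitivity row | listed | absent | listed, with multiple imputation |

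These entries do not lead to a single primary test.

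**3. Can a rank test and a mean difference disagree?** Illustrative simulation with assumed shapes, 83 per arm, 4,000 trials. In one arm 90% of patients score around 0.88 (SD 0.06) and 10% around 0.30 (SD 0.10). In the other arm scores centre on 0.822 (SD 0.10). All scores are capped at 0.95. The means are 0.819 and 0.817, nearly equal. Wilcoxon rejected in 77% of trials, the Welch t-test in 6%. A significant p-value could stand beside a mean difference of about 0.002.

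**4. Type I error.** Simulations with 83 per arm, 8 surgeons, baseline correlation 0.5, surgeon intraclass correlation 0 to 0.10, and normal and skewed data (all assumed; 4,000 trials per setting):

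- t-test alone, Wilcoxon alone, or a normality pre-test followed by one of them: 4.0% to 5.4%.
- Regression on arm, baseline and surgeon: 4.1% to 5.8%.
- Smallest p-value of t-test, Wilcoxon and that regression: 7.4% to 10.4%.

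Leaving surgeon out cost little. At intraclass correlation 0.10 the unadjusted tests ran at 4.0% to 4.9%, which is at most mildly conservative.

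**5. What adjustment would add.** With correlation r between baseline and week 12, the residual SD is 0.16 × √(1 − r²). Power at 83 per arm is Φ(0.07 / [residual SD × √(2/83)] − 1.96).

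| r (assumed) | Residual SD | Power at 83 per arm | n per arm for 80% |
|---|---|---|---|
| 0 | 0.160 | 80.5% | 83 |
| 0.3 | 0.153 | 84.0% | 75 |
| 0.5 | 0.139 | 90.2% | 62 |
| 0.6 | 0.128 | 94.1% | 53 |

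This normal formula gives 80.5% at r = 0, where the t calculation gives 80.0%.

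**6. Power of Wilcoxon.** On normal data its relative efficiency is 3/π = 0.955, so 83 per arm acts like 83 × 0.955 = 79.3. Power is about 78.6%, against 80.5% by the same formula. In a simulated left-skewed utility with a pure shift it was about 97%, against 80% to 82% for the t-test and 88% to 90% for the adjusted regression.

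**The case against.** The strongest reply is that regression is in the primary row and the methods text provides multivariable linear regression, which estimates a mean difference. This stands. A reader might infer that the comparison rests on an unadjusted Wilcoxon test, or that baseline and surgeon are excluded. The article supports neither: the covariates are unnamed, not ruled out. It condenses a fuller protocol, and a SAP may list them, so the missing list alone is not a fault.

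A reader might also infer that the trial is underpowered or that its type I error is inflated. Neither follows. The 80% reproduces, each single test holds close to 5%, and nothing says that the most favourable p-value will be reported. The 7.4% to 10.4% shows what a fixed choice rules out; it does not describe the plan.

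Nor does the case against Wilcoxon rest on power. Its loss on normal data is about 2 percentage points, and on skewed data it can win. The 97% is flattering, though: that simulation moves the upper limit of the scale from 0.95 to 0.95 + 0.07 = 1.02, above the value of 1 that the article assigns to full health. Wilcoxon's limitation here is the quantity it tests.

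On the order of baseline steps, participants are blinded, the questionnaire is self-reported and the coordinator gives minimal help. The sentence may simply be compressed. No bias has been shown, and the Trial status section says Phase A recruitment and follow-up are almost complete, so a change can only help participants still to be enrolled.

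What the reply does not answer is the conflict between the methods text and the two Table 3 rows, or the mismatch between a rank test and the mean difference used for sizing and reporting. A SAP could settle the choice, but these published statements would still disagree.

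**Conclusion.** The concern holds as a matter of specification. The primary row leaves the test open and conflicts with the t-test default in the text and the t-test's place under sensitivity. If Wilcoxon is chosen, the p-value will not test the mean difference of 0.07 on which the sample size rests. These points come from the text alone.

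The sample size is sound. Adjusting for baseline would raise power from 80% to about 84%, 90% or 94% at assumed correlations of 0.3, 0.5 or 0.6. This is precision available from data already collected, and its size depends on a correlation the article does not give. The simulated results also rest on assumed shapes, number of surgeons and intraclass correlations. They show direction and rough scale only.

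The change is worth making because it removes an open choice and needs no further patients. It does not call the trial's design into question.

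**What to change.** 1. Before anyone sees unblinded Phase A data, replace the primary method in Table 3 with one analysis, for example: *linear regression of week-12 EQ-5D-5L utility on arm, baseline utility and surgeon; adjusted mean difference with 95% CI and two-sided p-value.* Set in advance how surgeons with very few patients are handled.
2. Move the Wilcoxon test to the sensitivity row. Align the general methods text and the Primary analysis section, so that the t-test/Wilcoxon rule does not govern the primary outcome.
3. Date the change and record that it preceded unblinding. If outcome data by arm have already been seen, say so.
4. Minor: have the baseline questionnaire completed before the randomization step for participants still to be enrolled.

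Cost: wording in Table 3, two text sections and any SAP, plus the order of one visit step. Neither the planned 186 participants nor the data collected change.

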**SECONDARY**			
Short-Term Clinical Outcomes			
*Pathological Staging*	Improved	Pathological stage	McNemar’s test
*Lymph nodes*	More	Number of lymph nodes harvested	Independent t-test, Wilcoxon rank sum test/linear regression
*Duration of chest tube drainage*	Shorter	Number of days between surgery and chest tube removal	Kaplan-Meier method, Cox regression
*Hospital length of stay*	Shorter	Number of days between admission and discharge	Kaplan-Meier method, Cox regression
*Intra-operative blood loss*	Less	Volume of Intra-operative blood loss (mL)	Independent t-test/Wilcoxon rank sum test/ linear regression
*Post-operative analgesia requirements*	Less	In-hospital consumption (days, type, amount)	Independent t-test/Wilcoxon rank sum test/linear regression
*Chronic post-surgical pain*	Less	In-hospital pain (daily, scale)	Independent t-test/Wilcoxon rank sum test/ANOVA
Patient-reported Health-Related Quality of Life (HRQOL) outcomes	Improved	HRQOL scores, measured by the EQ-5D-5L at 3 and 7 weeks, and 6 and 18 months, and 1,2, 3, 4 and 5 years	Examine the distributions/ regression/ANOVA
Resource Utilization and Cost Effectiveness	More	Resource utilization tracking system, EQ-5D-5L, Return to Normal Living Index (RNLI), and employment status at 12 months	Incremental cost per quality-adjusted life year (QALY) gained will be calculated
Overall Survival	Improved	5-year survival difference	Kaplan-Meier method and cox proportional hazard models. Survival curves will be compared using the Log-rank test

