In the face of these barriers, a randomized controlled trial comparing VATS-Lobectomy to RTS-Lobectomy is needed. Prospective randomization will eliminate the biases of retrospective data and will serve to determine whether there exists any advantages to HRQOL or patient outcomes in favour of RTS-Lobectomy over VATS-Lobectomy. Furthermore, through a prospective cost-utility analysis, this trial will provide the highest quality data to evaluate the true economic impact of robotic technology in thoracic surgery.

RTS-Lobectomy has only been recently introduced in Canada, and the volume of preliminary cases in our group (University of Toronto’s Toronto General Hospital (TGH) and McMaster University’s St. Joseph’s Healthcare Hamilton (SJHH)) is a reflection of this novelty. The first case was performed in May of 2011 at the TGH. In the first Canadian series of RTS for pulmonary resection for lung cancer, which included 167 completed cases performed at TGH and SJHH, analysis showed a median operative time of 270 minutes (233–326), a very low rate of conversion to thoracotomy (12/167, 7.2%) and a median hospital length of stay (LOS) of 4 days (3–6) [8]. To measure the effects of the learning curve, the data was stratified by surgeon and evaluated in temporal tertiles. Total operative time decreased significantly (p<0.001) over the learning curve; tertile 1: 309.0 min, tertile 2: 258.5 min and tertile 3: 236.0 min. Median time spent on the robotic console also decreased significantly (p<0.001) over tertiles– 172.0, 136.0, and 116.0 minutes, respectively [8]. Across tertiles, there were no differences in the median number of lymph node stations harvested (8, 8, 8; p = 0.39), length of stay (4, 4, 4; p = 0.16), or the rate of major intraoperative complications (Clavien-Dindo Class ≥ III; 8, 2, 8, respectively; p = 0.28). There were no mortalities.

The early Canadian experience with robotic lung cancer resection demonstrates excellent results that are comparable to those of experienced centers in operative times, length of stay and conversion rates, with further improvement demonstrated by the learning curve effect (Table 1).

**Table 1 pone.0261767.t001:** Outcome comparison between the first 167 cases of RTS-Lobectomy.

	Tertile 1	Tertile 2	Tertile 3
Operative time (minutes)	309.0	258.5	236.0
Time on robotic console (minutes)	172.0	136.0	116.0
Conversion (no., %)	2 (3.0)	2 (4.3)	7 (14.0)
Nodes harvested (no.)	8	8	8
Length of Stay (days)	4	4	4

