#### Secondary objectives

In Phase A of this trial, we will compare differences in short-term clinical outcomes, and HRQOL outcomes at weeks 3 and 7; and months 6 and 12, which coincide with the intervals of oncological surveillance. We will also compute resource utilization and calculate the incremental cost effectiveness between RTS-Lobectomy and VATS-Lobectomy.

In Phase B of this trial, we will compare the difference in the 5-year survival data between the two arms. We will also compare differences in HRQOL outcomes at months 18 and 24; and years 3, 4, and 5, which coincide with the intervals of oncological surveillance. We will also compute resource utilization and calculate the incremental cost effectiveness between RTS-Lobectomy and VATS-Lobectomy.

RTS-Lobectomy is a new technology that has not been studied extensively yet against VATS-Lobectomy, so equipoise still exists. However, based on preliminary data from our experience and from literature, we hypothesize that for short-term clinical outcomes, RTS-Lobectomy leads to higher quality pathological staging by improved lymphadenectomy, and is associated with shorter duration of chest tube drainage; shorter hospital length of stay; less intraoperative blood loss; lower postoperative analgesia requirements; and less chronic postsurgical pain as compared to those who receive VATS-Lobectomy.

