#### Hospital stay data collection

Hospitalization data including hospital admission date, hospital discharge date, chest tube removal date, intraoperative blood loss, and postsurgical pain will be collected. During the hospital stay, the pain will be assessed with the Numeric Pain Rating Scale (NPRS) on movement (deep breathing or mobilization) and analgesic consumption will be collected daily starting with postoperative day 1, until the date of discharge, and the videotape of the surgery will be collected. Pathology details will be collected including the number of lymph nodes harvested, pathology stage and histology. Direct costing data will also be collected (e.g., equipment used, surgical disposables used, staff in operating room, number of days in step down or intensive care unit, medications used). In addition, prior to discharge, participants will be asked to complete the Trial Health Questionnaire.

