#### Trial health questionnaire

The Trial Health Questionnaire includes questions on the participant’s employment status, social activities (e.g., smoking, alcohol use), pain assessment (Numeric Pain Rating Scale) and two surveys, the EQ-5D-5L [16] and the Reintegration to Normal Living Index (RNLI) [17].

The NPRS is a numeric version of the visual analog scale, with 0 representing no pain and 10 representing the worst pain the participants can imagine. Participants will be asked to indicate their pain on movement (deep breathing or mobilization). The EQ-5D-5L has been validated for a number of chronic conditions, including cardiovascular and respiratory disease. The EQ-5D-5L is comprised of a descriptive system as well as a visual analog scale that assesses dimensions related to mobility, self-care, usual activities, pain/discomfort, and anxiety/depression. Respondents are asked to report their health states by rating each dimension as one of five levels (no problems, slight problems, moderate problems, severe problems and extreme problems). The RNLI is a self-report questionnaire used to evaluate global function status of a patient during rehabilitation which was developed to qualitatively assess the ability of individuals with traumatic or incapacitating illnesses to reintegrate into normal life. The RNLI is a questionnaire that is comprised of 11 questions that assesses mobility, self-care, daily activity, recreational activity, and family roles. Reintegration to normal living was defined as the reorganization of physical, psychological, and social characteristics of an individual into a harmonious whole so that one can resume well-adjusted living after incapacitating illness or trauma [18]. Each domain contains a visual analogue scale. On one end: “does not describe my situation” (1 or minimal integration) and “fully describes my situation” (10 or complete integration). Individual item scores are summed to provide the total score. The higher the score, the better the patients perceived integration.

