### Secondary analysis

Short-term clinical outcomes will involve aspects of perioperative care:
○ A higher quality of pathological staging is expected to occur with participants who have RTS-Lobectomy. Data on clinical and pathological staging will be compared.○ More lymph nodes are expected to be sampled for participants who have RTS-Lobectomy. The number of lymph nodes sampled for each patient will define the outcome measure.○ A shorter duration of chest tube drainage is expected to occur for participants who have RTS-Lobectomy. This will be measured by the number of days between the date of surgery and the date of chest tube removal.○ A shorter hospital length of stay is expected to occur for participants who have RTS-Lobectomy. This will be measured by the number of days between the date of hospital admission and the date of discharge.○ Less intraoperative blood loss (mL) is expected to occur for participants who have RTS-Lobectomy. This will be measured by the volume of blood loss in mL intraoperatively for each patient.○ Less post-operative analgesia requirements are expected to occur with participants who have RTS-Lobectomy. This will be measured by collecting the amount of analgesia consumed by each participant (e.g., type of medication used (e.g., PCA, epidural, intravenous, oral), the number of days the medication was used, and the amount used) in hospital.○ Less post-surgical pain is expected to occur in participants who have RTS-Lobectomy. This will be measured by collecting the pain score for each participant daily during their hospital admission.Resource Utilization and Cost Effectiveness

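### The Table 3 outcome labelled chronic post-surgical pain is measured only by daily in-hospital scores, so as defined it captures acute pain and cannot test the chronic-pain hypothesis

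*Protocol article*

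**What the plan says.** Under Secondary objectives, the protocol article lists its directional hypotheses for short-term clinical outcomes. One is that robotic lobectomy leads to "less chronic postsurgical pain as compared to those who receive VATS-Lobectomy". Table 3 carries this as a secondary row, "Chronic post-surgical pain", with the expected direction given as less. The outcome column of that row reads "In-hospital pain (daily, scale"), to be analysed by t-test, Wilcoxon test or ANOVA.

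The Secondary analysis section describes the pain outcome without the word chronic: "This will be measured by collecting the pain score for each participant daily during their hospital admission". Hospital stay data collection sets the window. The pain score on movement "will be collected daily starting with postoperative day 1, until the date of discharge".

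The Outcomes section also speaks only of post-surgical pain among the short-term clinical outcomes. In its list of cost variables, however, it tracks the costs of chronic post-surgical pain for as long as one year after the operation.

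The Trial Health Questionnaire includes "pain assessment (Numeric Pain Rating Scale) and two surveys". It is completed at baseline, before discharge and at every follow-up assessment.

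**The concern.** The label and the hypothesis concern chronic pain, while the measure covers only the days between surgery and discharge. If the plan is followed literally, a difference in early postoperative pain would be reported in the row for chronic pain, and readers would take it as evidence on a long-term outcome that had not been examined. A null result could mislead in the same way: similar pain in hospital says nothing direct about pain months later.

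The scores that could address the hypothesis are collected at follow-up, but no pain outcome in the article uses them. With several follow-up visits and none named for pain, a time point chosen after the data are seen would be post hoc.

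**Working it through.** The plan states no figure to reproduce here. The check sets the relevant statements side by side.

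1. **What is hypothesised.** Secondary objectives: less chronic pain with robotic surgery. Table 3 repeats the label and the direction.

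2. **What is measured.** Table 3: in-hospital pain, daily. Hospital stay data collection: from postoperative day 1 to discharge.

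3. **How long that window is.** Background and rationale gives, for the robotic series, "a median hospital length of stay (LOS) of 4 days (3–6"), and for the VATS series a median of 4 days. The scores therefore typically come from about the first 4 days, with 3 to 6 days as the quoted spread in the robotic series.

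4. **What time scale the document itself gives chronic pain.** The article does not define chronic pain. Its only time frame is the cost item, which runs to one year. A series that ends after a few days does not overlap with most of that period.

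5. **What else is collected.** The numeric pain scale, asked on movement, is in the Trial Health Questionnaire. Follow-up assessments are at weeks 3, 7 and 12 (three), months 6 and 18 (two) and years 1 to 5 (five): 3 + 2 + 5 = 10 time points after discharge. Five of these (weeks 3, 7 and 12, months 6 and 12) fall within Phase A follow-up. A baseline score is available because the questionnaire is also completed at enrolment.

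6. **How far apart the two time scales are.** Follow-up is counted from discharge, so the 12-week visit is 12 × 7 = 84 days after the in-hospital series has ended. Against the upper quoted stay of 6 days, that is 84 / 6 = 14 times the length of the in-hospital window.

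7. **Whether any stated analysis bridges the gap.** The general statement that ANOVA will be used for repeated measures does not, because the Table 3 row limits its outcome to in-hospital scores. The Secondary analysis text has the same limit. No other row in Table 3 names the follow-up pain scores.

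The label and hypothesis (step 1) and the measure (steps 2 and 3) therefore describe different outcomes.

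**The case against.** The strongest reply is that this is a slip of one word. The Outcomes section, Hospital stay data collection and Secondary analysis all describe post-surgical pain in hospital. The hypothesis itself sits in a list of short-term outcomes, and the stated objective is to compare short-term outcomes. On that reading, deleting the word chronic reconciles everything. This is a fair reading and one of the two acceptable remedies. It does not remove the point: the word stands in both the hypothesis and the analysis table, and one side or the other has to change.

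It can also be said that the article condenses a fuller protocol and that an analysis plan may assign the follow-up scores. That limits what can be said about those scores, but not the main point. Table 3 does not leave the measure open; it states one that contradicts its own label.

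A reader might infer more than the document supports:

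- **That the trial cannot address chronic pain at all.** It can, because the follow-up scores are collected. Only the outcome as defined cannot.
- **That the arms will be averaged over different postoperative days because robotic patients are expected to leave earlier.** The article does not say that scores are averaged over the stay, and day-by-day or repeated-measures comparison fits the text equally well. The group's own median stay is 4 days for both techniques, so its figures show no differential window.
- **That no information on pain after discharge will be reported.** The EQ-5D-5L has a pain/discomfort dimension, and the plan describes the EQ-5D-5L profile at follow-up. That is not a chronic-pain outcome, but it is not nothing.
- **That the one-year cost item lacks a necessary clinical counterpart.** It is a resource variable and does not need one.

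**Conclusion.** The point stands as an internal contradiction: an outcome named chronic pain is defined by scores from roughly the first 4 days after surgery. As written, the row would report acute pain as chronic pain, and the chronic-pain hypothesis has no outcome in this document that tests it.

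The scope is limited to one secondary outcome. The primary EQ-5D-5L comparison, both sample sizes, the survival analysis and the QALY calculation are untouched. It should be fixed, but it does not threaten the trial's main conclusions.

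The conclusion assumes only that pain confined to the hospital stay is not chronic pain in any ordinary sense, which agrees with the one-year horizon the article uses for chronic-pain costs. The 4-day figure comes from the group's earlier series; stays in the trial may differ, but not by enough to change the conclusion.

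**What to change.** First decide whether chronic pain is intended as an outcome.

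- **If it is:** relabel the existing Table 3 row as acute in-hospital postoperative pain. Add a separate row for chronic post-surgical pain, defined as the numeric pain score on movement from the Trial Health Questionnaire at one named follow-up time point. That could be 12 weeks or later, such as 6 or 12 months. Compare the arms with adjustment for the baseline pain score. Amend the Secondary analysis text to describe both outcomes.
- **If it is not:** remove the word chronic from the hypothesis in Secondary objectives and from the Table 3 row, so that no conclusion about chronic pain is drawn from in-hospital scores.

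Either change should be dated and made before arm-level results are seen. The analysing biostatistician is to work with coded groups, and Phase A results are to be reported only after the 12-month follow-ups, which helps to keep the choice independent of the results.

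The cost is a change of wording in two or three places and no new data collection. The real downside is that the first option redefines a secondary outcome when Phase A recruitment and follow-up are, by the article's own account, almost complete. The report should therefore state when and why the definition was set.
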